## 9. Treatment

### 9.1 Study treatment

#### - Investigational Product

The investigational product rituximab will be stored in a secure area according to local regulations. It will be the responsibility of the investigator to ensure that investigational product is only

dispensed to study subjects. The investigational product will be dispensed only from official study sites by authorized personnel according to local regulations.

Rituximab will be delivered at two different doses according to the arm of the protocol: 1g J0 and J15 in the personalized arm with anti-CTLD1/7 activity or 375 mg/m^2 J0 and J7 in the personalized arm with anti-CysR activity and active disease at M6 or in the GEMRITUX arm with active disease.

#### **- Packaging and Labeling**

Celltrion® / Biogaran® will provide Rituximab (Truxima®) at no cost for this study. Rituximab will be provided in open-label containers. The labels will contain the protocol prefix, batch number, content, storage conditions, and dispensing instructions along with the Investigational New Drug (IND) caution statement.

#### **- Handling and Dispensing**

The product storage manager will ensure that the study drug is stored in accordance with the environmental conditions (temperature, light, and humidity) as determined by Celltrion®/ Biogaran®. If concerns regarding the quality or appearance of the study drug arise, the study drug will not be dispensed and Celltrion®/ Biogaran® will be contacted immediately.

Investigational product documentation will be maintained and include all processes required to ensure drug is accurately administered. This includes documentation of drug storage, administration and, as applicable, storage temperatures, reconstitution, and use of required processes (e.g., required diluents, administration sets).

Investigation/non-investigational products that are procured as local marketed product should be stored in accordance with the package insert, summary of product characteristics (SmPC) or equivalent document.

Rituximab vials will be stored at a temperature of 2°C to 8°C and will be protected from light. If stored in a glass front refrigerator, vials will be stored in the carton. Recommended safety measures for preparation and handling of rituximab will include laboratory coats and gloves.

The investigational sites are responsible for providing IV bags, diluents, filters etc.

For details on prepared drug storage and use time of Rituximab under room temperature/light and refrigeration, please refer to the Investigator Brochure section for “Recommended Storage and Use Conditions.”

Care will be taken to assure sterility of the prepared solution as the product does not contain any anti-microbial preservative or bacteriostatic agent.

Rituximab will be delivered after the first randomization in the center if the patient is in PMMN arm.

2 treatments of Rituximab will be sent between 2°C and 8°C with specific transporter.

Rituximab will be to be administered IV infusion, using a volumetric pump start at 100 mg/h then increase to 400 mg/h. The drug can be diluted with 0.9% normal saline or glucosal 5% for delivery but the total drug concentration of the solution cannot be below 1 mg/ml. It is not to be administered as an IV push or bolus injection. At the end of the infusion, flush the line with a sufficient quantity of normal saline.

Rituximab could be associated with perfalgan 1g IV, Polaramine 5 mg and Solumedrol 100 mg.

## **9.2 Medical treatment common to both arms of the study: Nephro-protective treatment**

The KDIGO 2012 recommendations for the management of nephrotic syndrome will be followed:

First line RAAS blockade with an angiotensin-converting enzyme inhibitor (ACEI) or an angiotensin 2 receptor antagonist and diuretic up-titration.

Double RAAS blockade could be indicated under close monitoring.

Drugs employed for the symptomatic treatment are those uses in usual practice. Each center will be referring to the internet website: <http://base-donnees-publique.medicaments> for adapting the contraindications, contraception, monitoring of patients and prohibit drugs in accordance with the study (annexe 1).

## **9.3 Concomitant Treatments**

### **- Prohibited and/or Restricted Treatments**

Immunosuppressive agents or immunosuppressive doses of systemic corticosteroids are prohibited during the study (unless utilized to treat a drug related adverse event).

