| 
Randomized, open label, multicentre (22 centres), prospective trial comparing the efficacy of two therapeutic strategies to obtain clinical remission 1 year after diagnosis of iMN with nephrotic syndrome and anti-PLA2R1 antibodies:
 
 
- GEMRITUX protocol: 6 months of symptomatic antihypertensive and antiproteinuric therapy, and if the nephrotic syndrome persists at month-6 (urinary protein/creatinine ratio (UPCR) remains > 3.5 g/g and albuminemia < 30 g/l), two 375 mg/m^2 rituximab infusions at 1-week interval.
 
- Personalized treatment: 
 
o restricted anti-CysR activity at inclusion: 6-month symptomatic antihypertensive and antiproteinuric treatment (KDIGO)
 
o restricted anti-CysR activity after 6 months of symptomatic treatment with persisting nephrotic syndrome (UPCR remains > 3.5 g/g and albuminemia < 30 g/l): two 375 mg/m^2 rituximab infusions at 1-week interval;
 
o Anti-CTLD1/7 activity at inclusion or after 6 months with persisting nephrotic syndrome (UPCR remains > 3.5 g/g and albuminemia < 30 g/l): two 1g rituximab infusions at 2-week interval at month 0 and/or month 6. For patients who will develop anti-rituximab antibodies, treatment with human anti-CD20 is widely recommended.
 
 
 
 |

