#### **M6 visit = 6 months after randomization +/-15 days**

- Consultation date
- Clinical examination: weight, blood pressure, edema
- Serious adverse events
- Changes in concomitant treatments
- Blood and urine lab results
- Estimated GFR CKD EPI
- Centralized assays for both arms:
  - 2 dry tubes of 5 ml of blood and 2 EDTA tubes of 3 ml of blood will be shipped to Nice at room temperature for PLA2R1-Ab, epitope profile determination, serum rituximab levels, anti-rituximab antibodies, and, B and T cells counts (see manual lab)
- **In the GEMRITUX arm**
  - If disease still active (UPCR remains > 3.5 g/g and albuminemia < 30 g/l): plan two 375 mg/m^2 Rituximab infusions at 1-week interval (+/- 2 days) between 5 and 14 days after M6 visit.
  - If remission (partial or complete, see p.12): symptomatic treatment to be continued.
- **In the personalized arm/ Patients who received RTX at M0**
  - If remission (partial or complete, see p.12): symptomatic treatment to be continued alone and contraception will be required during 12 months after the end of the treatment.
  - If disease still active / Restricted anti-CysR activity: plan two 375 mg/m^2 rituximab infusions at 1-week interval (+/- 2 days) between 5 and 14 days after M6 visit.

- if disease still active / Anti-CTLD1/7 activity: plan two 1g rituximab infusions at 2-week interval (+/- 2 days) between 5 and 14 days after M6 visit. For patient who will develop anti-rituximab antibodies, treatment with human anti-CD20 is widely recommended.

*NB: If the patient still active disease / anti-PLA2R1 Ab-; the symptomatic treatment should be optimized*

- **In the personalized arm/ Patients who received 6-month symptomatic treatment**

- If remission (partial or complete, see p.12): symptomatic treatment to be continued
- If disease still active / Restricted anti-CysR activity: plan two 375 mg/m^2 rituximab infusions at 1-week interval between 5 and 14 days after M6 visit.
- if disease still active / Anti-CTLD1/7 activity: plan two 1g rituximab infusions at 2-week interval between 5 and 14 days after M6 visit.

**For all:** plan M9 +/-15 days and hand out a prescription to the patient for blood and urine analyses\*

\* Blood sample: urea, creatinine, electrolytes (sodium, potassium, chloride, bicarbonate), protein, albumin, full blood count.

Spot morning urine sample: protein, albumin, urea, creatinine.

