### **At the first relapse**

If the patient presents a still active disease with anti-PLA2R1 and anti-rituximab activity, the following cares are left to the investigator's discretion due to the Rituximab contraindication. However, the patient must perform the following visits according to the protocol.

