#### **10.10 Withdrawal of Study Participants**

The researchers may decide to withdraw the patient from the study if:

- The medical problem becomes worse.
- The researchers believe that participation in the research is no longer safe for the patient.
- The researchers believe that other treatment may be more helpful.
- The sponsor or the EMA stops the research for the safety of the participants.
- The sponsor cancels the research.
- The patient is unable to keep appointments or to follow the researcher's instructions.

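### Section 9.3 bans a drug that the protocol recommends elsewhere, and section 10.10 allows outcome-dependent withdrawal from the study without securing later visits

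*Protocol*

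**What the plan says.** Section 9.3, under prohibited treatments, sets a ban for the whole study with one exception: "Immunosuppressive agents or immunosuppressive doses of systemic corticosteroids are prohibited during the study (unless utilized to treat a drug related adverse event". The permitted-therapy text that follows adds exceptions for corticosteroids only.

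Three other places point the other way. The Summary (experimental plan) and section 2.1 both say: "For patients who will develop anti-rituximab antibodies, treatment with human anti-CD20 is widely recommended". The M6 visit text in section 8.5 repeats it, for personalised-arm patients who had rituximab at M0: "For patient who will develop anti-rituximab antibodies, treatment with human anti-CD20 is widely recommended". Section 9.1 names no study drug other than rituximab: "Rituximab will be delivered at two different doses according to the arm of the protocol".

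*At the first relapse* deals with patients whose disease is still active and who have both anti-PLA2R1 and anti-rituximab activity. For them, "the following cares are left to the investigator's discretion due to the Rituximab contraindication", followed by "However, the patient must perform the following visits according to the protocol".

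Section 10.10 opens its list with "The researchers may decide to withdraw the patient from the study if". The first ground is "The medical problem becomes worse"; another is the researchers' belief that a different treatment would serve the patient better. The section has no sentence on visits or data collection after withdrawal.

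**The concern.** There are two separate defects, and both lie in protocol text that governs what sites do.

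The first is a contradiction. A site that gives a human anti-CD20 as recommended breaches 9.3, and a site that respects 9.3 sets the recommendation aside. Sites may settle this differently. It is also unclear which arm the recommendation covers: the M6 text places it under the personalised arm, while section 2.1 places it after the description of the control strategy.

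The second is that two of the withdrawal grounds depend on how the patient is doing, and they are judged by investigators who know the arm (section 4: open label). If the visits of such patients stop, the data are missing for reasons tied to outcome. That affects the primary endpoint when withdrawal comes before M12, the M18 and M24 comparisons when it comes later, and the 24-month recording of adverse events (section 2.2, objective 9) in either case. An analysis plan can choose how to handle missing visits, but it cannot recover them.

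**Working it through.** The point rests mainly on setting the rules side by side.

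**Ban against recommendation**

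| Question | Where | Answer |
|---|---|---|
| How long does the ban run? | 9.3, prohibited | The whole study |
| Which exceptions exist? | 9.3, prohibited and permitted | Treating a drug-related adverse event; certain corticosteroid uses |
| Is a human anti-CD20 study treatment? | 9.1 | No; only rituximab is listed, and no human anti-CD20 is named, dosed or timed |
| What would it be given for? | Summary, 2.1, M6 visit | The nephropathy, once rituximab is compromised by antibodies |

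A human anti-CD20 is therefore a non-study immunosuppressant given for the disease, and neither exception reaches it. The two rules cannot both be followed.

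**Ban against *At the first relapse***

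This text leaves care open but names no immunosuppressant, so it could mean discretion within the ban. That reading would leave a patient with active disease and contraindicated rituximab without any immunosuppressive option. It is a possible conflict, softer than the first.

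**Withdrawal rule**

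1. Section 10.10 speaks of leaving the study, not of stopping treatment.
2. Worsening disease and a preferred alternative treatment are both judgements about outcome.
3. The only sentence that keeps patients in visits after a change of care is the one under *At the first relapse*. It covers only active disease with both kinds of antibody.
4. Sections 8.4 and 8.5 schedule rituximab only at M0 and M6. A patient with active disease at M12 who is outside that subgroup has no written route to further immunosuppression except withdrawal under 10.10.
5. Visits at stake per patient, from the schedule of assessments: withdrawal just after M6 puts four at risk (M9, M12, M18, M24); withdrawal just after M12 puts two at risk (M18, M24).

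**Scale for the primary endpoint**

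- Planned size (section 7.2): 2 × 29 = 58, and 58 × 1.10 = 63.8, so 64 in total. With 1:1 allocation that is 32 per arm.
- One patient is 1/32 = 3.1 percentage points of an arm's remission rate. The planned difference is 80% − 45% = 35 points.
- Section 12.1 carries the last observation forward for a missing primary outcome. A patient withdrawn between M6 and M12 as a non-remitter, who would have been in remission at M12, lowers that arm's rate by 3.1 points. In the control arm this widens the difference; in the personalised arm it narrows it. A withdrawn patient who would not have remitted changes nothing.

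The protocol gives neither the number withdrawn, nor their later course, nor the number with anti-rituximab antibodies, so the sum of these effects cannot be computed.

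**The case against.** **The ban was never meant to reach treatment the protocol itself directs.** Section 9.3 concerns concomitant treatment; read literally it would also ban rituximab, so the specific recommendation should prevail over the general ban. This is a fair reading, and it makes the contradiction easy to cure. It does not remove it: rituximab is defined as study treatment in 9.1, a human anti-CD20 is not, and 9.3 writes out its exceptions without including it.

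**Section 10.10 is optional and does not say that data collection stops.** That is correct. A reader might infer that it orders follow-up to end, and the text does not support that. What stands is narrower: nothing in it secures the later visits, although the protocol does secure them for one subgroup. Analysis by assigned arm (section 12.1) does not replace the missing data.

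**Withdrawals will fall mainly on the control arm and favour the personalised arm.** A reader might infer this from expected M12 non-remission of 32 × 0.55 = 17.6 control against 32 × 0.20 = 6.4 personalised patients. The documents do not support it. Non-remission is not worsening: control patients first receive rituximab at M6, and section 1.3 reports a median of 9 months to remission on that regimen, so many would still be nephrotic at M12 on the expected course. Nor are these counts a ceiling. They leave out patients active between M6 and M12 who later remit, and patients who relapse after remission (7 of 34 in section 1.4).

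**Follow-up of serious events continues anyway.** Section 10.5 covers related serious events that the investigator learns of after the trial ends. It does not provide for collection at visits.

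**Conclusion.** The point holds in two parts. The conflict between 9.3 and the human anti-CD20 recommendation is a direct contradiction; the conflict with the relapse text is only possible. Section 10.10 permits outcome-dependent loss of M12, M18 and M24 data and of safety follow-up, because it does not separate ending treatment from leaving the study. The size and direction of any resulting bias cannot be derived from the protocol. The only firm figure is the scale of 3.1 points per altered M12 outcome, assuming 32 patients per arm. The case for change rests on the wording and on the small cost of correcting it, not on a computed bias.

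**What to change.** (a) In section 9.3, add an exception for human anti-CD20 in patients with documented anti-rituximab antibodies, in either arm, and for care given under *At the first relapse*. Leave the ban otherwise unchanged. It should not be worded to lapse when protocol treatment ends: starting a banned drug would then lift the ban, possibly before M12, in an open-label comparison.

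(b) In section 10.10, state that worsening disease or a need for other treatment ends protocol treatment only, and that in both arms the patient continues all visits and safety collection to M24 unless consent is withdrawn. How such patients are counted can be left to the analysis plan.

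The cost is amendment wording in two sections and a small number of extra visits: two per patient concerned after M12, up to four for one concerned just after M6. No new data field is needed, since the permitted-therapy text in 9.3 already requires medications started during the study to be documented.

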### **- Permitted therapy**

Subjects are permitted the use of topical, ocular, intra-articular, intranasal and inhalational corticosteroids (with minimal systemic absorption). Physiologic replacement doses of systemic corticosteroids are permitted even if > 10 mg daily prednisone (or equivalent). A brief course of corticosteroids for the prevention (e.g., for contrast dye allergy) or treatment of non-autoimmune conditions (e.g., delayed-type hypersensitivity reaction caused by a contact allergen) is permitted. Concomitant medications are recorded at screening/baseline and throughout the treatment phase of the study, in the appropriate section of the CRF. All medications (prescriptions or over the counter

medications) continued at the start of the study or started during the study and different from the study drug must be documented in the concomitant therapy section of the CRF.

## 10. Reporting adverse events (AEs) and serious adverse events (SAEs)

### 10.1 Definitions

|                             |                                                                                                                                                                                                                                                                                                                                                                                                                                                                                                                                                                                                             |
|-----------------------------|-------------------------------------------------------------------------------------------------------------------------------------------------------------------------------------------------------------------------------------------------------------------------------------------------------------------------------------------------------------------------------------------------------------------------------------------------------------------------------------------------------------------------------------------------------------------------------------------------------------|
| Adverse Event (AE)          | Any untoward medical occurrence in a participant to whom a medicinal product has been administered, including occurrences that are not necessarily caused by or related to that product.                                                                                                                                                                                                                                                                                                                                                                                                                    |
| Adverse Reaction (AR)       | 
An untoward and unintended response in a participant to an investigational medicinal product, which is related to, any dose administered to that participant.
 
The phrase "response to an investigational medicinal product" means that a causal relationship between a trial medication and an AE is at least a reasonable possibility, i.e. the relationship cannot be ruled out.
 
All cases judged by either the reporting medically qualified professional or the Sponsor as having a reasonable suspected causal relationship to the trial medication qualify as adverse reactions.
 |
| Serious Adverse Event (SAE) | 
A serious adverse event is any untoward medical occurrence that:
 
 
Results in death
 
Is life-threatening
 
Requires patient hospitalisation or prolongation of existing hospitalisation
 
Results in persistent or significant disability/incapacity
 
Consists of a congenital anomaly or birth defect.
 
                                                                                                                                                                                                                |

|                                                       |                                                                                                                                                                                                                                                                                                                                                                                                                                                       |
|-------------------------------------------------------|-------------------------------------------------------------------------------------------------------------------------------------------------------------------------------------------------------------------------------------------------------------------------------------------------------------------------------------------------------------------------------------------------------------------------------------------------------|
|                                                       | 
Other ‘important medical events’ may also be considered serious if they jeopardise the participant or require an intervention to prevent one of the above consequences.
 
NOTE: The term "life-threatening" in the definition of "serious" refers to an event in which the participant was at risk of death at the time of the event; it does not refer to an event, which hypothetically might have caused death if it were more severe.
 |
| Serious Adverse Reaction (SAR)                        | An adverse event that is both serious and, in the opinion of the reporting Investigator, believed with reasonable probability to be due to one of the trial treatments, based on the information provided.                                                                                                                                                                                                                                            |
| Suspected Unexpected Serious Adverse Reaction (SUSAR) | 
A serious adverse reaction, the nature and severity of which is not consistent with the information about the medicinal product in question set out:
 
In the case of a product with a marketing authorisation, in the summary of product characteristics (SmPC) for that product
 
In the case of any other investigational medicinal product, in the investigator’s brochure (IB) relating to the trial in question.
               |

NB: to avoid confusion or misunderstanding of the difference between the terms “serious” and “severe”, the following note of clarification is provided: “Severe” is often used to describe intensity of a specific event, which may be of relatively minor medical significance. “Seriousness” is the regulatory definition supplied above.

